#### Analysis procedures

Statistical analysis will be performed using SPSS 16.0 (SPSS Inc., Chicago, IL, USA) at the Clinical Evaluation Center of Shanghai General Hospital, Shanghai Jiao Tong University School of Medicine.

#### Sample distribution

The size and dropout rate for each dataset will be described. Clarified reasons for any participant’s withdrawal from the trial will be provided.

#### Baseline information

Baseline adjusted analyses will be provided for center and severity variables, and the baseline value of the corresponding outcomes will be assessed. Descriptive statistics will be used to compare baseline measures with participant characteristics. If an imbalance occurs in baseline characteristics between the two groups, analysis of covariance will be applied.

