#### Primary outcome measure

Change in TNSS will be measured for each participant by comparing the baseline score with the score at the end of the 4-week treatment. TNSS is determined by the severity of rhinorrhea, nasal pruritus, nasal obstruction, and sneezing.

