### Statistical analysis

#### Sample size calculation

The trial will test two groups in parallel. Sample size calculation was performed using SAS 9.3 (SAS Institute Inc., Cary, NC, USA) at the Clinical Evaluation Center of First People’s Hospital Affiliated to Shanghai Jiaotong University. The mean change in TNSS before and after treatment was used as the indicator of efficacy evaluation in sample size calculation. Other research has shown a mean TNSS change of 2.53 ± 4.74 after acupuncture treatment [22] and 2.75 ± 1.06 after AAP [35]. Based on these findings, the appropriate trial sample size with power of 80%, alpha value of 0.05, and acceptable delta value of 0.2 was calculated. The results show that a clinically important difference can be detected by a sample size with at least 49 in each group. Accordingly, this number was increased to 60 per group (a total of 120) to allow for a predicted 20% dropout rate.

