#### Efficacy analysis

Efficacy data analyses will be conducted on an intention-to-treat population. All participants initially included in any group will be considered in statistical analysis. Analysis of efficacy will be performed per-protocol and will include all participants who complete the entire research. Descriptive statistics will be used to compare serum indicators between the two groups. Regarding the primary and secondary outcome measures, a two-sample *t* test or Wilcoxon rank-sum test will be used to compare differences between both groups from baseline to the end of treatment (*p* < 0.05 will be considered statistically significant). The mean and standard deviation values of these parameters will be reported. Regarding repeated measures data, repeated measures analysis of variance will be performed after meeting spherical symmetry requirements. SPSS 16.0 will be used for all statistical calculations.

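### The plan does not say which analysis of week-4 TNSS change is primary, and it ties ANCOVA to an undefined baseline imbalance instead of always adjusting for baseline TNSS

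*Protocol article*

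**What the plan says.** The primary outcome is a change score: "Change in TNSS will be measured for each participant by comparing the baseline score with the score at the end of the 4-week treatment" (Primary outcome measure).

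Three statements then bear on how it is tested.

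- Efficacy analysis offers an unadjusted two-sample t test as one option, and otherwise: "Wilcoxon rank-sum test will be used to compare differences between both groups from baseline to the end of treatment". The threshold is p "< 0.05 will be considered statistically significant". No rule for choosing between the two tests is given.
- Baseline information opens without any condition: "Baseline adjusted analyses will be provided for center and severity variables, and the baseline value of the corresponding outcomes will be assessed".
- The same section ends with a condition: "If an imbalance occurs in baseline characteristics between the two groups, analysis of covariance will be applied". It gives no list of variables, no threshold and no criterion for imbalance.

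Table 1 shows TNSS collected at W0, before treatment. The Missing data analysis section says that an independent statistician will write a detailed analysis plan.

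**The concern.** A reader cannot tell from these sections which result will be reported as the primary one: the unadjusted test, the analysis adjusted for center and severity, or an ANCOVA that may or may not be run. The outcome's own baseline value, usually the most useful covariate, is only to be assessed; it is not clearly put into a model.

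The trigger is a separate weakness. Under 1:1 randomisation, any baseline difference is due to chance. Whether adjustment sharpens the comparison depends on how well baseline predicts outcome, and that is the same whether or not the arms happen to differ. At stake are precision, if the unadjusted test becomes primary, and the credibility of the primary p-value, if the route to it can be settled after the data are seen.

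**Working it through.** **Inputs.** From the article: 1:1 allocation, a change-score outcome, p < 0.05 (taken as two-sided, since sidedness is not stated), and 49 per group before dropout. Not in the article, hence assumed: the baseline/week-4 correlation r, equal SDs at the two times, normal data, and the size of the effect.

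**The plan's own figure.** The 49 per group cannot be reproduced from the stated inputs ("the appropriate trial sample size with power of 80%, alpha value of 0.05, and acceptable delta value of 0.2 was calculated"). With the two quoted SDs, 4.74 and 1.06, the pooled SD is √[(4.74² + 1.06²)/2] = 3.43. Then n = 2 × (1.96 + 0.84)² × 3.43² / 0.2² gives 4,630 per group (with unrounded terms). That is a separate matter. Here 49 only sets a scale: the effect is fixed at the value that gives the change-score test 80% power with 49 per arm, which is 0.566 SD of the change.

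**Step 1: variance ratio.** With SD σ at both times, the per-participant variances are:

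- change score: 2σ²(1 − r)
- ANCOVA residual: σ²(1 − r²)
- ratio: (1 − r²) / [2(1 − r)] = (1 + r)/2

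**Step 2: what the ratio means at 49 per arm.** Let f = (1 + r)/2. ANCOVA power is Φ(2.80/√f − 1.96), and the equivalent sample size is 49 × f, rounded up.

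| r (assumed) | f | Variance saved | ANCOVA power when the change-score test has 80% | n per arm for 80% |
|---|---|---|---|---|
| 0.3 | 0.65 | 35% | 93% | 32 |
| 0.5 | 0.75 | 25% | 90% | 37 |
| 0.7 | 0.85 | 15% | 86% | 42 |
| 0.9 | 0.95 | 5% | 82% | 47 |

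**Step 3: does a conditional rule recover the gain?** The article defines no rule, so one was assumed: ANCOVA if baseline TNSS differs at p < 0.05, otherwise the change-score t test. Simulation used 40,000 trials per setting and 49 per arm.

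| r | Power: t test on change | Power: ANCOVA always | Power: conditional rule | Type I error: conditional rule | Type I error: smaller p of t and ANCOVA |
|---|---|---|---|---|---|
| 0.3 | 79.4% | 93.0% | 80.8% | 4.1% | 7.8% |
| 0.5 | 79.4% | 89.1% | 80.4% | 4.3% | 7.1% |
| 0.7 | 79.2% | 85.3% | 79.8% | 4.5% | 6.7% |

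At r = 0.3 the rule gains 80.8 − 79.4 = 1.4 points out of a possible 93.0 − 79.4 = 13.6, about a tenth. The other rows give a similar share. This is expected: under randomisation the trigger fires in about 5% of trials.

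**Step 4: type I error.** A second simulation of the same fixed rule gave 4.3% to 4.7%, so it stays at or below 5%. A looser trigger, baseline p < 0.2, gave 3.2% to 4.3%. Only choosing freely after the fact raises the error: keeping the smallest p of t, Wilcoxon and ANCOVA gave 7.7% to 8.5% across two separate simulations at r = 0.3 to 0.7.

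**The case against.** Four points can be made for the plan.

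- **Adjustment is planned.** A reader of the conditional ANCOVA sentence might infer that baseline is adjusted for only when the arms look unequal. The opening sentence of the same section does not support this, since it promises adjusted analyses without condition. The ANCOVA sentence can even be read as adding covariates to those. This stands: the defect is an unresolved conflict over which analysis is primary, not a plan without adjustment.
- **The unadjusted test is valid.** Under randomisation a change-score comparison is unbiased. This also stands; the loss is one of efficiency. The loss depends on unknown quantities and could be small. With unequal SDs the ratio becomes (1 − r²)/(1 + k² − 2rk), where k is baseline SD over follow-up SD, and it reaches 1 when k = r. The exclusion of TNSS below 4 may narrow the baseline spread.
- **Type I error.** A reader might infer that the imbalance rule itself inflates false positives. It does not, as Step 4 shows, and nothing in the article says that the smallest p-value will be reported.
- **Detail belongs in the analysis plan.** The choice between t and Wilcoxon, the covariate list and the definition of imbalance are commonly left there, so their absence alone is no fault. But the article does write down the trigger and two competing analyses. An analysis plan that followed the article would carry the conflict forward; one that corrected it would depart from the article.

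**Conclusion.** The point holds as a conflict to be resolved and an inefficient rule to be removed. The Baseline information and Efficacy analysis sections do not settle which analysis of week-4 TNSS change is primary, and the stated trigger for ANCOVA does not track when adjustment helps. Adjusting in every case would cut variance by 35%, 25%, 15% or 5% at r = 0.3, 0.5, 0.7 or 0.9, if baseline and follow-up SDs are equal; a conditional rule of the kind simulated recovers almost none of this. The true r, the SD ratio and the effect size are not in the article, so the loss in this trial is unknown within that range or smaller. Type I error is about 4% to 4.7% under a fixed rule at baseline p < 0.05. The figure of about 8% is a worst case that applies only if the analyst is free to keep the best of three tests. This should be corrected, but it does not invalidate the trial.

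**What to change.** Name one primary analysis: ANCOVA of week-4 TNSS change on group, baseline (W0) TNSS and center, in all randomised participants, whatever the observed balance. Report the adjusted mean difference with its 95% CI. Using change or the week-4 score as the response gives the same treatment estimate once baseline is in the model.

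Keep the t or Wilcoxon test as a sensitivity analysis, delete the sentence that makes ANCOVA depend on imbalance, and state that the promised adjustment for severity is supportive. Make the change in both the protocol and the analysis plan before unblinding. The cost is wording only, since TNSS at W0 and center are already collected.

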#### Efficacy analysis

Efficacy data analyses will be conducted on an intention-to-treat population. All participants initially included in any group will be considered in statistical analysis. Analysis of efficacy will be performed per-protocol and will include all participants who complete the entire research. Descriptive statistics will be used to compare serum indicators between the two groups. Regarding the primary and secondary outcome measures, a two-sample *t* test or Wilcoxon rank-sum test will be used to compare differences between both groups from baseline to the end of treatment (*p* < 0.05 will be considered statistically significant). The mean and standard deviation values of these parameters will be reported. Regarding repeated measures data, repeated measures analysis of variance will be performed after meeting spherical symmetry requirements. SPSS 16.0 will be used for all statistical calculations.

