Acupuncture is a component of traditional Chinese medicine (TCM) that was originally believed to work on the principle of the redistribution of qi, the life energy. In TCM, disease is understood to originate from an imbalance or poor flow of qi. Acupuncture has long been used in TCM to treat AR, and studies of this treatment have shown mixed results, with the most rigorous studies showing only modest clinical benefits [21–24]. The 2015 revision of the American Academy of Otolaryngology-Head and Neck Surgery clinical practice guidelines for AR cites a low level of confidence in the evidence to support acupuncture as a treatment option. Acupuncture may be a reasonable option for patients with relatively mild symptoms who wish to minimize medication use and who find its cost acceptable [1]. These results have helped practitioners to improve their use of acupuncture to treat AR. However, high-quality scientific evidence is needed to instruct the clinical application of acupuncture.

Preliminary experiments have found that the use of acupuncture at three nasal acupoints plus acupoint application (AAP) achieve a more persistent effect in the treatment of AR than simple acupuncture alone. Based on this preliminary research, a multicenter, randomized controlled trial (RCT) has been designed in which acupuncture at nonmeridian acupoints and sham AAP will be used with a control group to evaluate the effect of AAP through long-term observation. The purpose of this trial is to answer three questions: (1) Does AAP benefit PAR? (2) How long do the effects last? and (3) Does AAP work by intervening peripheral blood IL-4, IL-5, IL-6, IL-8, and IL-10 levels? Similar research techniques have been applied in previous studies on PAR such as the Total Nasal Symptom Score (TNSS) [25], visual analog scale (VAS) [26], and Total Non-Nasal Symptom Score (TNNSS) [22]. This trial has adopted TNSS, VAS, and TNNSS due to their wide applicability. The trial hypothesis is that AAP will achieve equal or better long-term symptom relief in PAR or severe AR and reduce its recurrence compared to acupuncture alone.

The trial has been registered at acmctr.org AMCTR-ICR-18000179.

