#### Secondary outcome measures

Changes in TNSS will be measured by comparing the baseline score with the score at 2 weeks and 1, 3, and 6 months after treatment. VAS and TNNSS will be used to observe supplementary symptoms and severity of symptoms. These will also be evaluated at 2 and 4 weeks and 1, 3, and 6 months after treatment. Peripheral blood IL-4, IL-5, IL-6, IL-8, and IL-10 levels will be measured by Luminex to observe allergic reactions.

All outcome readings will be scored on quantitative scales and summarized as mean values and standard deviation.

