#### Quality control

Before recruitment, the entire research staff involved in the trial including acupuncturists, operational assistants, and research nurses must receive training in advance. Training will include the method for correctly filling out CRFs, blood tests, details of AAP, use of scales, participants’ method of using the medication diary, and follow-up visit skills. Researchers will be examined after training to ensure strict adherence to the trial protocol and consistency of the trial administration process including acupuncture and AAP treatment and evaluation method. The entire research staff will be provided with a written protocol and standard operating procedure documents. All acupuncturists who apply the treatment must have acupuncture licenses from the Ministry of Health of People’s Republic of China and > 5-year clinical experience.

To improve the quality of trial reporting and conduct, we will develop a standard operating procedure manual according to the principles of the CONSORT Extension for Chinese Herbal Medicine Formulas [33] and will thoroughly train all investigators. Intervention details such as acupuncture rationale, needling details, treatment regimen, time selection, practitioner background and confidence, and adequacy of stimulation were extracted and evaluated by CZ and SX according to STRICTA [34].

To ensure data authenticity, a special research team from the Clinical Research Center of Shanghai General Hospital, Shanghai Jiao Tong University School of Medicine, independent of the investigators and sponsors, will externally monitor the trial at the three hospitals every 3 months. An advisory board will follow the trial and provide advice when necessary.

To improve intervention adherence, free treatment and blood tests will be provided to the treatment group for 4 weeks. To ensure that treatment and follow-up run on schedule, participants will be assured of and given monetary compensation at the end of the follow-up period.

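### The protocol gives the five cytokines two conflicting analyses, descriptive in one sentence and tested at 0.05 in the next, and neither answers the trial's third question soundly

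*Protocol article*

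**What the plan says.** All references are to the protocol article.

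- **Background.** "The purpose of this trial is to answer three questions", and the third is "Does AAP work by intervening peripheral blood IL-4, IL-5, IL-6, IL-8, and IL-10 levels". The Discussion repeats this aim as whether the treatment can affect these levels.
- **Secondary outcome measures.** The cytokines are listed here: "Peripheral blood IL-4, IL-5, IL-6, IL-8, and IL-10 levels will be measured by Luminex to observe allergic reactions". No other blood outcome is named.
- **Efficacy analysis.** One sentence reads "Descriptive statistics will be used to compare serum indicators between the two groups". The next opens "Regarding the primary and secondary outcome measures" and names a two-sample t test or a rank test: "Wilcoxon rank-sum test will be used to compare differences between both groups from baseline to the end of treatment", with p < 0.05 as the threshold. It makes no exception for the cytokines.
- **Baseline information (under Statistical analysis).** Baseline-adjusted analyses are mentioned, and analysis of covariance is planned if the groups are imbalanced at baseline.
- **Quality control.** To support adherence, "free treatment and blood tests will be provided to the treatment group for 4 weeks".
- **Missing data analysis.** A detailed statistical analysis plan by an independent statistician is announced. It is not shown.

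**The concern.** Two adjacent sentences give the same outcomes two different analyses. A descriptive comparison produces neither an interval nor a test for the difference between groups. A test at 0.05 on each of five cytokines produces a p-value for each, and this text does not say how the five are read together. While the choice stays open, it can be made after the data are seen, and a single nominally significant cytokine could be presented as evidence of mechanism.

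At stake is one of the three stated purposes of the trial. The primary outcome, change in TNSS at 4 weeks, is untouched.

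**Working it through.** The plan gives no figure for the cytokine analysis, so there is none to reproduce. The check compares the text and then sizes each reading.

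**1. Do both sentences cover the cytokines?** The article does not define serum indicators. The cytokines are the only blood outcome it lists, so taking the term to mean them is a reasonable inference. They stand under the secondary outcomes heading, so the testing sentence covers them as well. The two rules overlap and nothing ranks them.

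**2. If the descriptive sentence governs.** Specific text is usually taken to override general text, so this is a natural reading. The third question then gets summary values per group and no inference.

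**3. If the testing sentence governs.** Inputs are five cytokines and a threshold of 0.05 each.

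- Independent tests: 1 − (1 − 0.05)^5 = 1 − 0.95^5 = 0.226, or 22.6%.
- Equally correlated normal test statistics, by simulation: about 0.18 at a correlation of 0.5 and about 0.15 at 0.7.

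The documents give no correlation between cytokines, so 0.5 and 0.7 are assumptions. Correlated cytokines are likely, so 22.6% is illustrative.

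**4. What would baseline adjustment gain?** The testing sentence compares differences from baseline, so the right comparator is the change score. Let the variance σ² be equal at both times and ρ be the correlation between baseline and end of treatment. Then:

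- change score: 2σ²(1 − ρ)
- ANCOVA: σ²(1 − ρ²)
- ratio, ANCOVA to change score: (1 + ρ)/2

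| ρ (assumed) | Ratio | Variance reduction |
|---|---|---|
| 0.3 | 0.65 | 35% |
| 0.5 | 0.75 | 25% |
| 0.7 | 0.85 | 15% |

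**5. Is an inferential comparison workable at this size?** The detectable standardised difference is (z_alpha + z_power) × √(2/n). With 80% power and a two-sided test (the article does not state sidedness):

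- n = 49 per group: (1.960 + 0.842) × √(2/49) = 0.57 SD at 0.05; (2.576 + 0.842) × √(2/49) = 0.69 SD at 0.05/5 = 0.01.
- n = 60 per group: 0.51 SD and 0.62 SD.

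The group size does not rule out a between-group estimate. The obstacle is the conflicting text.

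**6. Is blood taken in both groups?** The descriptive sentence compares the two groups, which needs samples from both. Quality control mentions free blood tests for the treatment group alone. Table 1 has no cytokine row. Fig. 2, which is said to show all evaluation time points, is not reproduced in the text available, so missing sampling times are not held against the plan. The mismatch over which group receives blood tests still needs to be reconciled.

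**The case against.** A fair defence has four parts.

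- **The plan does name a test.** A reader might infer from the descriptive sentence that the cytokines are only described and that the third question cannot be answered. The documents do not support that: the next sentence applies a t test or Wilcoxon test to all secondary outcomes. What remains is that the two sentences conflict.
- **Baseline and distribution are not ignored.** A reader might also infer that the tests disregard baseline. They do not: they compare differences from baseline, and baseline-adjusted analyses are mentioned elsewhere. That cytokine values will be skewed is not documented, and the Wilcoxon option partly covers it. Both points stand, so log scaling is conditional.
- **Multiplicity for secondary markers is commonly left to the analysis plan.** This stands as far as a missing rule goes, and the absence of one here is no fault by itself. It does not excuse two incompatible rules in the protocol's own text. No passage says that one nominal p-value would carry the mechanism claim; that is a risk of leaving the choice open.
- **A comparison of levels would not show mechanism either.** The third question asks whether the treatment works through the cytokines, which is mediation. This stands, and the question's wording should be narrowed.

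A reader might further take the Quality control sentence to mean that controls are not sampled. The planned two-group comparison implies that they are, so the text supports only a request for confirmation.

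**Conclusion.** The point holds as an internal contradiction about a secondary outcome that carries one of the trial's three questions. Under the specific rule that question has no inferential answer. Under the general rule there are five tests at 0.05 with no multiplicity rule in this text, and a chance of at least one false positive of 22.6% if independent, or about 15 to 18% at assumed correlations of 0.7 to 0.5.

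This rests on reading serum indicators as the five cytokines. The gain from ANCOVA over change scores further assumes equal variances at the two times. The unseen analysis plan may settle which rule applies, but it does not remove the conflict in the protocol. The correction is worth making because it is cheap.

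**What to change.** Replace the descriptive sentence with one between-group analysis, for example:

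> Each cytokine at the end of treatment will be compared between groups by ANCOVA with its baseline value and centre as covariates, on the log scale if the values are skewed, and reported as an estimate with a 95% confidence interval.

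Then:

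1. Exempt the cytokines from the general testing sentence, so that one rule applies.
2. State either that the five comparisons are Holm-adjusted or that they are exploratory and cannot alone support a claim about mechanism.
3. Reconcile the Quality control sentence with the two-group comparison by confirming that both groups are sampled at baseline and at the end of treatment.
4. Reword the third question as an effect on cytokine levels, since this analysis does not test mediation.

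The cost is a few lines of wording and no new assay, provided both groups are already sampled. If controls are not sampled, the cost is larger, because the article says recruitment has begun. With Holm, the smallest of the five p-values must fall at or below 0.01, so the threshold per cytokine is stricter. The exploratory option avoids that but gives up a confirmatory claim.

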**Fig. 1 Fig1:**
[figure not shown]
CONSORT flow diagram

To achieve the targeted enrollment of participants, clinical recruitment flyers will be placed at three hospitals. Clinical recruitment staffs are responsible for enrolling 120 participants with moderate-to-severe PAR. Participants will be screened based on inclusion and exclusion criteria. All participants will be briefed on the purpose, procedures, treatments, and possible risks of the trial; and will be clearly informed of their rights to discontinue participation at any point. Screening will take approximately 1 week. During this period, participants will be asked to complete questionnaires related to their symptoms. Once participants have signed consent forms, they will be randomized to receive 12 sessions of AAP or sham acupuncture and AAP for 4 weeks.

The trial design flowchart is presented in Fig. 1, and the trial design schedule is shown in Table 1.

**Table 1 Tab1:** Trial design schedule

Period	Screening	Baseline	Treatment(W1–4)		Follow-up(W5-M6)	
Time	W-1	W0	W2	W4	M3	M6
Eligibility	X					
Demography and medical history	X					
Physical examination	X					
Informed consent	X					
TNSS	X	X	X	X	X	X
VAS	X	X	X	X	X	X
TNNSS	X	X	X	X	X	X
Adverse event			X	X		
Medication use	X	X	X	X	X	X
Compliance			X	X	X	X

*TNSS* Total Nasal Symptom Score, *VAS* visual analog scale, and *TNNSS* Total Non-Nasal Symptom Score

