### Trial participants

The trial will recruit inpatients from the three trial locations admitted from January 2018 to June 2020. To ensure that results are accurate, the trial will include strict inclusion, exclusion, and elimination criteria, as outlined below.

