#### Missing data analysis

All data used in the main statistical analysis should be collected by the fourth week of the treatment and by the 6-month follow-up. To avoid missing data, participants who complete the trial and provide completed data will be financially compensated. The investigators have a wealth of experience from previous trials in managing participants and collecting data. Participant contact information will be recorded and researchers will keep in touch with them through various means of communication during the treatment and follow-up periods.

If data are not obtained, the time and reason for missing data will be recorded and the assumed missing data mechanism will be analyzed. For these missing data, a multiple imputation adjustment approach will be used. After the main analysis, sensitivity analysis will be performed for the various datasets to enable the assessment of the impact of missing data on the results.

A detailed statistical analysis plan will be written by an independent statistician.

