### Trial status

The recruitment of participants for this trial has begun. The trial is designed to be completed by June 30, 2020.

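### The question of how long the effect lasts has only a sphericity-conditional ANOVA behind it, Table 1 omits the 1-month visit, and the completion date is too early for late recruits to reach month 6

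*Protocol article*

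**What the plan says.** The Background section lists the duration of the effect as the second of three trial questions, and the Abstract singles out the long-term effect.

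- **Tests.** Under Efficacy analysis, a two-sample t test or Wilcoxon rank-sum test "will be used to compare differences between both groups from baseline to the end of treatment". The section then adds: "Regarding repeated measures data, repeated measures analysis of variance will be performed after meeting spherical symmetry requirements". It says nothing about what happens if the requirement is not met.
- **Who is analysed.** The same section names an intention-to-treat population and then says: "Analysis of efficacy will be performed per-protocol and will include all participants who complete the entire research". The Follow-up section removes participants who discontinue or deviate, together with their latest outcome data. The Missing data analysis section says: "For these missing data, a multiple imputation adjustment approach will be used".
- **Visits.** Secondary outcome measures compares baseline TNSS with "the score at 2 weeks and 1, 3, and 6 months after treatment". The Abstract and the Data collection and management section also list a 1-month assessment, and the Follow-up section describes monthly contact. In Table 1 the block headed "Follow-up(W5-M6" has columns for M3 and M6 only.
- **Dates.** Trial participants: "The trial will recruit inpatients from the three trial locations admitted from January 2018 to June 2020". Trial status: "The trial is designed to be completed by June 30, 2020". Each participant has 4 weeks of treatment followed by 6 months of follow-up.

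**The concern.** Persistence of benefit is the stated reason for the trial, since the pilot is cited for a more lasting effect. Read literally, the between-group test stops at week 4 and the later visits fall to an ANOVA that is run only if a covariance condition is met. If the condition fails, the article names no long-term comparison. If it holds, an omnibus group-by-time F test shows that the profiles differ somewhere, not whether the arms still differ at 1, 3 or 6 months.

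The data for that question are also at risk. A site working from Table 1 would not collect the 1-month scores, and late recruits could not have a month-6 score by the stated completion date.

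**Working it through.** The protocol gives no figure of its own for any of these points, so there is nothing to reproduce. The checks below are a simulation under assumed correlations and calendar arithmetic from stated dates.

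**1. How often would the sphericity condition fail?**

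Inputs from the protocol: 60 per group and 20% dropout, so 60 × 0.8 = 48 per group, 96 in all; six assessments (weeks 0, 2 and 4, then 1, 3 and 6 months after treatment, that is about weeks 0, 2, 4, 8.3, 17 and 30). Assumptions: the condition is judged by Mauchly's test at 5%, and the correlation structures are as listed, because the protocol states neither. Epsilon is the usual sphericity index (1 means it holds exactly).

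| Assumed structure | Epsilon | Mauchly rejects | Type I error of uncorrected group-by-time F test |
|---|---|---|---|
| Compound symmetry, correlation 0.3, 0.5, 0.7 | 1.00 | 5.5%, 4.4%, 4.8% | 4.8%, 5.0%, 5.4% |
| Compound symmetry 0.5, SD rising to 1.4 times baseline | 0.97 | 37% | 4.7% |
| AR(1) by visit order, 0.3, 0.5, 0.7 | not computed | 89%, 100%, 100% | not computed |
| Decay over actual spacing, 0.90, 0.95, 0.98 per two weeks | 0.53, 0.46, 0.42 | 100% in each | 9.2%, 8.2%, 9.7% |

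The AR(1) row used 1,000 runs and the other rows 3,000. The failure rate therefore runs from about 5% to 100%. Where serial correlation is present, running the ANOVA uncorrected would not be a safe way out: its type I error is about 8% to 10% rather than 5%.

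**2. Who would enter the ANOVA?**

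Classical repeated-measures ANOVA needs a score at every visit. At 20% dropout, 120 × 0.20 = 24 participants could lack one. Multiple imputation would keep them in. The completer analysis and the Follow-up exclusions would leave them out. The article contains all three statements and does not say which governs the long-term comparison.

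**3. The 1-month visit**

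| Place | Post-treatment assessments |
|---|---|
| Abstract (VAS, TNNSS) | 1, 3, 6 months |
| Secondary outcome measures | 1, 3, 6 months |
| Data collection and management | 1, 3, 6 months |
| Table 1 | 3, 6 months |

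**4. Calendar**

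- Last start that can reach month 6: 30 June 2020 − 6 months = 30 December 2019; − 28 days = 2 December 2019.
- If recruitment did run to 30 June 2020: + 28 days = 28 July 2020; + 6 months = 28 January 2021 for the last visit.
- Share affected, assuming uniform accrual from 1 January 2018 to 30 June 2020 (911 days): 2 December 2019 to 30 June 2020 is 211 days; 211 / 911 = 23.2%; × 120 = 27.8, about 28 participants without month 6.
- Month 3 on the same assumption: latest start 2 March 2020, 120 / 911 = 13.2%; × 120 = 15.8, about 16 participants.
- Week 4: latest start 2 June 2020, 28 / 911 = 3.1%; × 120 = 3.7, about 4 participants.

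**The case against.** Several stronger readings are tempting, and the other side is right to resist them.

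- *The later visits would have no analysis at all.* The protocol promises a detailed statistical analysis plan, which could hold a sphericity correction or a fallback. The sentence on the t and rank-sum tests also opens by naming primary and secondary outcomes, and the secondary outcomes include the later visits. So the article does not say that follow-up goes unanalysed. What stands is that its own wording stops the test at end of treatment and makes the only repeated-measures method conditional.
- *Sphericity will rarely hold.* No correlations are given. The high rejection rates come from assumed serial correlation; under compound symmetry the condition is rejected only at the nominal rate.
- *24 participants will be lost.* Imputation could retain them. The loss is possible but not established; the unresolved conflict between statements is what the text shows.
- *The 28 late recruits exceed the 20% dropout allowance.* That allowance was set for a sample size based on TNSS change before and after treatment, not for month-6 retention, so the two figures are not comparable. The 28 also depends on uniform accrual. The recruitment window may simply have been written as the whole study period.
- *The 1-month visit was dropped.* Three places in the text plan it, and Fig. 2, which is not shown, is said to give all time points. Table 1 looks like an omission. It still needs correcting, because it is the trial's schedule.

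**Conclusion.** The point holds as a weakness in how the long-term question is analysed, plus two internal contradictions. The analysis rule is poorly fixed because it makes the comparison depend on a covariance condition with an unknown chance of failing (about 5% to 100% across the structures tried), and because an omnibus test does not locate the visit at which a difference persists or fades. The Table 1 omission and the date conflict can be read directly from the document and do not depend on any analysis plan. The 2 December 2019 cutoff follows from the stated dates alone; the figures of 28 and 16 participants rest on uniform accrual.

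The week-4 primary comparison is not affected by the ANOVA rule or by Table 1. The date conflict would touch it only for anyone starting in the last four weeks. The changes should be made, but the primary result does not hang on them.

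**What to change.** 1. Replace the sphericity-conditional ANOVA with a mixed model for repeated measures: arm, visit, arm-by-visit interaction, baseline score and centre, unstructured covariance, all available post-baseline data. Report the between-group difference with a 95% CI at each visit. With five post-baseline visits the covariance has 5 × 6 / 2 = 15 parameters. The model needs neither sphericity nor complete visits, but it does assume that missing scores are missing at random. State that the week-4 primary test remains as planned.
2. Say which data enter this model, so that the intention-to-treat, completer, exclusion and imputation statements no longer pull apart.
3. Add the 1-month visit to Table 1.
4. Reconcile the recruitment and completion dates so that every participant can finish follow-up: either end randomisation by about 2 December 2019, or restate completion as about seven months (4 weeks plus 6 months) after the last randomisation.

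Testing the later visits in a fixed order is optional; its price is that a later visit cannot be claimed once an earlier one fails.

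The cost is a short change of analysis wording, one table column, and either an earlier accrual stop or a later completion date.
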